# COVEPIC (Cognitive and spOrt Virtual EPIC training) investigating the effects of home-based physical exercise and cognitive training on cognitive and physical functions in community-dwelling older adults: study protocol of a randomized single-blinded clinical trial

**DOI:** 10.1186/s13063-021-05476-2

**Published:** 2021-07-29

**Keywords:** Aging, Cognition, Cognitive training, Physical exercise, Remote monitoring, Home-based training, COVID

## Abstract

**Background:**

In the context of the COVID-19 pandemic, lockdown and social distancing measures are applied to prevent the spread of the virus. It is well known that confinement and social isolation can have a negative impact on physical and mental health, including cognition. Physical activity and cognitive training can help enhance older adults’ cognitive and physical health and prevent the negative collateral impacts of social isolation and physical inactivity. The COVEPIC study aims to document the effects of 6 months of home-based physical exercise alone versus home-based physical exercise combined with cognitive training on cognitive and physical functions in adults 50 years and older.

**Methods:**

One hundred twenty-two healthy older adults (> 50 years old) will be recruited from the community and randomized to one of the two arms for 6 months: (1) home-based physical exercises monitoring alone and (2) combined physical exercises monitoring with home-based cognitive training. The primary outcome is cognition, including general functioning (Montreal Cognitive Assessment (MoCA) score), as well as executive functions, processing speed, and episodic memory (composite *Z*-scores based on validated neuropsychological tests and computerized tasks). The secondary outcome is physical functions, including balance (one-leg stance test), gait and mobility performance (Timed Up and Go, 4-meter walk test), leg muscle strength (5-time sit-to-stand), and estimated cardiorespiratory fitness (Matthews’ questionnaire). Exploratory outcomes include mood, anxiety, and health-related quality of life as assessed by self-reported questionnaires (i.e., Geriatric depression scale-30 items, Perceived stress scale, State-trait anxiety inventory-36 items, Perseverative thinking questionnaire, Connor-Davidson Resilience Scale 10, and 12-item Short Form Survey).

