### Hypotheses

After 6 months of home-based physical exercise, participants will show an improvement in cognitive (primary outcome) and physical functions measures (secondary outcomes), with larger gains in executive functions.Participants in the combined home-based physical exercise and cognitive training group will show greater improvements in cognition and physical functions post-intervention compared to participants who did not complete the cognitive training.

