#### Primary outcome—Cognition

Cognitive functioning will be assessed via videoconference, using validated remote versions of paper-pencil neuropsychological assessments [37] and computerized tasks, both performed under the supervision of a research team member. G*eneral cognitive functioning* will be tested using a remote version of the Montreal Cognitive Assessment (MoCA) [38]. The remote version of the MoCA is identical to the original version, to the exception that one question in the orientation subscale is modified (“Now, tell me the name of this place, and which city it is in” was replaced by one question regarding an important sightseeing place in Canada). In addition, the *three main components of cognition* will be assessed with a comprehensive neuropsychological assessment, including both paper-pencil tests and computerized tasks, from which composite z scores will be calculated: executive functions, processing speed, and episodic memory. These different composite *Z*-scores will first be computed by grouping tests and subscores that conceptually assess the same cognitive functions (mean of *z*-scores of different tests and scores). In a second step, internal consistency among each composite *z*-score will be verified with Cronbach’s alphas as done previously (*α* > .7) [39]. The neuropsychological assessment will include the following paper-pencil tests that will be administered in a fixed order: Rey auditory verbal learning test [40], Digit Span, an oral Trail Making Test with three conditions (1—counting from 1 to 20 (maximum of 30s); 2—naming letters from A to Z (maximum of 30 s); 3—alternating between naming numbers and letters in chronological and alphabetical order (e.g., 1-A-2-B) (maximum of 30 s) [41]), Phonological and Semantic Fluency from the D-KEFS battery (Letters P, T, L (60 s maximum); Categories: animals, men’s names (60 s maximum); Switching between naming fruit and furniture (60 s maximum) [42]), and Similarities subtest from the WAIS-IV [43]. These tests are validated and normalized for an older adult population [40, 44, 45]. The Similarities subtest will only be administered at baseline to obtain a measure of crystallized intelligence; it will be optional and performed according to the level of the participant’s fatigue. Participants will also complete a computerized assessment on their tablet or computer [32]. The computerized tasks include a dual-task [32], Stroop task [33], and N-back [34], all in trained and transfer versions (same tasks but with different stimuli) presented in a counterbalanced order between the participants via a Latin square procedure. Subcomponents of each task allow the dissociation of attentional control mechanisms from mere cognitive speed. Importantly, the tasks record response time in milliseconds reducing the likelihood of ceiling effects. These tasks also tend to be more sensitive to training effects. The trained and transfer task comparison allows quantifying participants' ability to transfer cognitive training effects to another task. The computer equipment (i.e., computer or tablet) used by the participant for the computerized tasks will be systematically documented. Participants will be requested to use the same computer equipment for the four testing sessions.

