### Data analysis

#### Sample size calculation

The Montreal Health Innovations Coordinating Center**’**s biostatistics team completed the sample size calculation. The calculation was based on values available in the literature for physical exercise training alone [67], on different plausible values for the combined physical and cognitive training (since there are no values in the literature for this group), and on clinically relevant effect sizes to detect the cognitive outcome. A sample size of 49 subjects in each group will have 80% power to detect a difference in means of **−** 0.186 (the difference between a physical training alone mean of 0.239 and a combined training mean of 0.425, for an effect size of 0.624), assuming that the common standard deviation is 0.298 using a two-group *t* test with a 0.050 two-sided significance level. Considering a 20% attrition rate observed in our previous exercise studies, 61 participants will be recruited per intervention arm to ensure the targeted 49 participants per group (61 * .80 = 49) for a total of 122 participants.

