#### Planned data analysis

The variables in the study will be presented using descriptive statistics. The mean, standard deviation, median, minimum, Q1, Q3, and maximum will be presented for continuous variables. The number and percentage will be presented for nominal/ordinal variables. The statistical tests' assumptions will be examined, and data transformation or non-parametric analyses may be used as appropriate. SPSS and SAS version 9.4 or higher software will be used to conduct the analyses. Statistical tests will be two-tailed, and a *p* value of less than 0.05 will be considered as the indication of statistical significance.

Mean changes in cognitive performance from baseline will be analyzed using a repeated measures analysis of covariance (ANCOVA) model, adjusted for age, sex, education, and the dose of physical exercise, including the effects of the intervention (physical exercise alone or combined with cognitive training) and time (pre at baseline, mid at 3 months, post-intervention at 6 months). Observation of a statistically significant difference in the primary outcome between pre- and post-intervention timepoints will be considered as the evidence of the intervention's efficacy (i.e., primary hypothesis). The interaction between intervention arms (i.e., physical exercise alone or combined with cognitive training) and performance changes from pre to post-intervention will address the added value of the cognitive training compared to physical exercise alone (i.e., secondary hypothesis). Observation of a statistically significant *intervention × time* interaction in the primary outcome will be considered as the evidence that the differential effect operates by the exercises and combined interventions. Secondary and exploratory outcomes will be analyzed as the primary outcome.

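### Four measures together form the primary outcome, but the success rule and the sample size are written for one, and the article does not say whether any, all or one named measure must be significant

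*Protocol article*

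**What the plan says.** The Abstract (Methods) gives the outcome as follows: "The primary outcome is cognition, including general functioning (Montreal Cognitive Assessment (MoCA) score), as well as executive functions, processing speed, and episodic memory". The section on the primary outcome repeats the structure. The MoCA covers general functioning, and beside it stands a battery "from which composite z scores will be calculated: executive functions, processing speed, and episodic memory". Each composite is the mean of the z-scores of its own tests. No overall cognitive score is formed from the four, and no order among them is given.

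Planned data analysis sets one threshold for all tests: a p "value of less than 0.05 will be considered as the indication of statistical significance". It then gives two decision rules. For what it calls the primary hypothesis: "Observation of a statistically significant difference in the primary outcome between pre- and post-intervention timepoints will be considered as the evidence" of efficacy. For what it calls the secondary hypothesis, a significant intervention-by-time "interaction in the primary outcome will be considered as the evidence that the differential effect operates by the exercises and combined interventions". Both rules speak of the primary outcome in the singular.

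Sample size calculation uses a two-group t "test with a 0.050 two-sided significance level", with means of 0.239 and 0.425, a common SD of 0.298, 49 per group and 80% power. It refers only to a cognitive outcome and does not say which of the four it means.

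**The concern.** A success rule written for one variable is applied to four. A reader of the final report could not tell from the article whether one significant measure out of four makes the trial positive, whether all four are needed, or whether one of them was always the intended test. That choice would remain open after the data are seen.

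The sample size does not settle the matter. It is one test on an unnamed measure. It is also a comparison between arms, which the analysis section assigns to the secondary hypothesis, so the article's only power statement does not belong to the hypothesis it calls primary.

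Naming the primary outcome and the success criterion is protocol content, and here both are given. The difficulty is that they do not fit together.

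**Working it through.** **Inputs from the article.** Four primary measures (Abstract; Primary outcome). Two-sided alpha 0.05 per test (Planned data analysis). Means 0.239 and 0.425, SD 0.298, 49 per group, 80% power, 20% attrition, 61 recruited per arm (Sample size calculation).

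**Assumed.** Equal pairwise correlation r among the four test statistics, varied from 0 to 0.9, because the article gives none. For joint power, the same d = 0.624 on every measure.

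**1. The plan's own figure.**
- Difference: 0.425 − 0.239 = 0.186. Effect size: 0.186 / 0.298 = 0.624. Both reproduce.
- Exact two-sample t test (noncentral t, df = 2n − 2, noncentrality d√(n/2)): power is 79.7% at 41 per group, 80.7% at 42 and 86.4% at 49.
- The stated inputs therefore need 42 per group, not 49. The difference is on the safe side and is a separate matter. What follows uses 49 per group, where one test at 0.05 has 86.4% power.
- Attrition: 61 × 0.80 = 48.8, in line with the stated 49.

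**2. If any one of the four suffices.** With no true effect on any measure and independent tests, the chance of at least one false positive for one hypothesis is 1 − 0.95⁴ = 18.5%. For jointly normal test statistics this is the maximum. Simulation of four equicorrelated two-sided z tests (2 million draws per setting) gives:

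| r | P(at least one false positive) |
|---|---|
| 0 | 18.5% |
| 0.3 | 17.4% |
| 0.5 | 15.6% |
| 0.7 | 13.0% |
| 0.9 | 9.4% |

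**3. If all four are required.** The chance that all four are falsely significant cannot exceed that of any single one, so the error is at most 5%. Joint power falls instead. For independent tests it is 0.864⁴ = 0.557, about 56%. Simulated two-sample t tests with 49 per group and d = 0.624 on every measure give about 67% at r = 0.5 and 72% at r = 0.7. Even at r = 0.9 the result is about 78%, still below the stated 80%.

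**4. If all four stay primary with Bonferroni.** Alpha per measure is 0.05 / 4 = 0.0125.
- Power for one measure at 49 per group: 70.6%.
- For 80% power: 59 evaluable per group. With 20% attrition, 59 / 0.80 = 73.75, so 74 per arm and 148 in total, against the planned 122.

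**5. If one measure is primary.** Error is 5% and power at 49 per group is at least the stated 80%. This is the only reading under which the decision rule and the sample size agree, and the article does not say which measure it would be.

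**The case against.** The strongest reply is that the article never says any single significant measure is enough. A reader might infer such a rule from four listed measures and a flat 0.05, but the text speaks only of significance in the primary outcome and gives no rule for combining measures. That reply stands: the 18.5% is conditional on one reading and is not a property of the plan as written. A narrower range such as 13% to 19%, stated as fact, would also need correlations that the article does not report.

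A second reply is that multiplicity procedures usually sit in the analysis plan, which is not shown. This also stands in part. The absence of an adjustment from a journal article is not held against the trial here. The reply does not reach the core, because the article itself fixes four primary measures, one threshold, a singular success rule and a single-test sample size. An unseen plan would have to override or complete these.

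A reader might also pool the two hypotheses into eight tests and quote a larger error. The article ranks them as primary and secondary and does not present them as one family, so the figures here are per hypothesis.

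Finally, the executive composite may look like the obvious single primary. The Hypotheses section does expect improvement "with larger gains in executive functions", but only for the pre-post hypothesis. The between-arm hypothesis, on which the trial was sized, favours no domain. The scale of the sample-size inputs does not decide it either, since all three composites are z-scores. It is one candidate among several.

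**Conclusion.** The point holds as an undefined decision rule, not as a stated bad one. Four measures share primary status, and the article does not say whether any, all or one of them decides the trial. Under the any-one reading, error per hypothesis is at most 18.5% and falls to about 9% at a correlation of 0.9. Under the all-four reading, error is controlled but joint power is about 56% to 72% for correlations of 0 to 0.7. These figures rest on assumed equal correlations and, for power, on d = 0.624 for every measure. Because the gap bears directly on whether the trial can be called positive, it should be closed before the data are analysed.

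**What to change.** Before the data are analysed, choose one of two routes:

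- **One primary.** Name a single measure, or a global composite with its components and weighting defined in advance, at 6 months. The executive composite is one option. Test the remaining measures as key secondary outcomes in fixed order or with Holm.
- **Four primaries.** Keep all four and apply Holm or Bonferroni within each hypothesis. Restate the power: about 71% per measure at alpha 0.0125 with 49 per group and d = 0.624.

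Under either route, state which measure and which hypothesis the sample size refers to.

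The first route costs some outcomes their stand-alone primary status; the second lowers the stated power. Recruitment began in May 2020 and was due to end in August 2021, so this is a late change to a primary outcome. It should be recorded as a dated amendment with its reason, through the ethics board approval and published-record update that the article's Ethical considerations section already provides for. Adding Holm across the four disturbs the existing outcome list least.

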**Discussion:**

This trial will document the remote monitoring of home-based physical exercise alone and home-based physical combined with cognitive training to enhance cognitive and physical health of older adults during the COVID-19 pandemic period. Remote interventions represent a promising strategy to help maintain or enhance health and cognition in seniors, and potentially an opportunity to reach older adults in remote areas, where access to such interventions is limited.

**Trial registration:**

Clinical trial Identifier NCT04635462. COVEPIC was retrospectively registered on November 19, 2020.

## Background

The current COVID-19 pandemic resulted in unusual public health measures challenging the worldwide population's lifestyle. To limit the spread of the virus, confinement and social distancing measures are the cornerstone of most public health policies all around the world and are strongly recommended by the World Health Organization (WHO). Older adults represent a group at higher risk of hospitalization and death from COVID-19 [1–3], for whom social distancing measures are of paramount importance. However, refraining from outings for a long period implies an important reduction in social interactions and a substantial increase in physical inactivity and sedentary behaviors likely to impact the populations’ health. The negative psychological impacts of quarantine and lockdown have been recently documented [4, 5], and social isolation and loneliness (i.e., perceived social isolation) are known to be risk factors for anxiety, depression, and cognitive decline [6]. In older adults, social isolation and loneliness have also been associated with poorer cognitive functions [7]. Additionally, sedentary behaviors and physical inactivity are associated with an increased risk of cardiovascular events, rehospitalization, and decreased cardiorespiratory fitness [8, 9]. Consequently, the important changes in daily-life routine induced by the COVID-19 crisis may impact older adults’ health as they are more likely to be suffering from chronic conditions [10]. Therefore, adapted and effective solutions are needed to enhance physical health and cognition in seniors while maintaining social distancing during this pandemic period.

The Global Recommendations of the WHO, recently updated, state the importance of physical activity to promote health outcomes across the lifespan, highlight the fact that short bouts of physical activity are better than none, and provide new guidelines to reduce sedentary behavior [11]. Moreover, to fight against the mental and physical consequences of the COVID-19 pandemic, governmental health authorities, as well as the scientific community, recommend to stay physically active [8]. Multiple studies and meta-analyses suggest that physical activity and exercise have a positive impact on physical condition [12–14] and cognition [15–17], especially on executive functions [18, 19]. Recent evidence demonstrated that performing physical activity, even at low intensity, could help reduce some of the negative consequences of social distancing on older adults’ mental health [20]. In the current pandemic context, web-based and remote interventions are a promising solution, as they have previously demonstrated robust effectiveness in promoting physical activity [21]. In their systematic review, Gaeredts et al. [22] highlight the potential of remote training with a coach to promote physical activity and to enhance older adults' physical capacity. However, a limited number of studies have investigated the impact of long-term remote monitoring of physical exercise on physical and mental health, and the potential benefits on cognition have not been investigated. Moreover, the optimal dose of home-based physical exercise to promote older adults’ cognitive and physical health remains to be investigated, especially in a pandemic context likely to increase sedentary behaviors and social isolation.

Computerized cognitive training has also been used to enhance specific aspects of cognitive functioning in seniors [23]. Moreover, cognitive training seems to improve postural control [24] and mobility [25], suggesting that it can help enhance and maintain gross motor skills, including balance and mobility-related outcomes [25]. Physical activity and cognitive training are thought to involve different mechanisms of brain plasticity. Recent studies investigating the combined effect of physical exercise and cognitive training suggest that they exert synergistic effects on cognition [26, 27]. Hence, a combined intervention involving both home-based cognitive and physical training could lead to an even more pronounced improvement of cognitive health and mobility than physical exercise alone in older adults.

This study will investigate the benefits of monitoring home-based physical exercise combined with cognitive training in community-dwelling older adults and will explore the dose-response relationship (i.e., total amount of exercise including type, frequency, duration, and intensity) of home-based physical exercise for optimal cognitive and physical health benefits. More precisely, this trial aims to (1) document the effects of remote monitoring of home-based physical exercise on cognitive and physical functions in older adults, and (2) address the added benefits of a multidomain home-based intervention involving both cognitive training and physical exercise.

### Hypotheses

After 6 months of home-based physical exercise, participants will show an improvement in cognitive (primary outcome) and physical functions measures (secondary outcomes), with larger gains in executive functions.Participants in the combined home-based physical exercise and cognitive training group will show greater improvements in cognition and physical functions post-intervention compared to participants who did not complete the cognitive training.

## Methods/design

### Design

COVEPIC is a randomized, single-blind trial with two parallel intervention arms:
*Arm 1 – Physical exercise*: remote monitoring and counseling of home-based physical exercise.*Arm 2 – Physical exercise and cognitive training*: remote monitoring and counseling of home-based physical exercise and home-based cognitive training.

The study design includes six months of intervention. All participants will be assessed at baseline, 3 months, and 6 months. At each timepoint, four testing sessions will be done remotely using videoconference supervision and online questionnaires over a period of 7–10 days. At twelve months (6 months after the end of the intervention), a follow-up assessment will be performed to explore the potential maintenance of intervention effects. Participation in this follow-up assessment will be left to the participant's discretion, as it does not directly address the main hypotheses. The trial was designed according to SPIRIT guidelines (cf. SPIRIT checklist in the additional file) [28]. Figure 1 illustrates the trial design according to items of SPIRIT figure, which is also available in additional files.

